### Aims and objectives

This study arises from a commissioning call by the UK’s National Institute for Health Research and represents one component (Work Stream 2) of the wider project, LP-MAESTRO,^26^ which is designed to evaluate the cost-effectiveness and efficiency of liaison psychiatry service provision in the UK. The aim of the study described in this paper is to examine care pathways for the main target populations of liaison psychiatry services and estimate the outcomes and costs associated with care. Specifically, we will:

Use routinely collected NHS data to identify patients referred to specific liaison psychiatry services and matched comparison patients who were not referred, with the aim of comparing within and between hospitals the effect of referral or non-referral of patients with similar characteristics.Estimate the cost of the care pathways of patients referred to liaison psychiatry services, and the matched comparison patient groups, and the main determinants of those costs over 12 months after an index hospital episode.

We will characterise patients according to their contact with liaison psychiatry service, for example reason for referral, scheduled or urgent referral and mental health diagnosis. We will determine those patients who were referred to liaison psychiatry services from acute (general hospital) sources, and a matched sample of cases from the same sources who were not referred. We will compare outcomes for certain marker conditions (such as mental–physical comorbidity, acute behavioural disturbance, cognitive impairment/dementia) in different liaison psychiatry service configurations.

### Data sources

Patient data that are relevant to the study are routinely collected by clinicians and healthcare professionals to inform patient care. Such data are collected independently by the organisations that provide different services to patients, and only those variables that are required to fulfil the purpose(s) of these services are included. A limited number of standardised data sets are collected from organisations that provide care and are aggregated at national-level by organisations, such as NHS Digital. Some of these data sets (or derivatives) are made available for research purposes. However, no single organisation can currently provide the data that are required for the study, so linkage is essential.

Hospital Episode Statistics (HES)^27^ is a database controlled by NHS Digital that contains patient data relating to ED, inpatient and outpatient episodes for NHS hospitals in England. Episodes represent discrete periods of care under a particular consultant. Episodes can be combined into spells to represent the period of care from admission to discharge. HES is derived from the Commissioning Data Set,^28^ which is supplied to NHS Digital by organisations that provide NHS services to facilitate monitoring and payment. Patients can opt-out of the inclusion of their *confidential patient information* in data sets which are made available by NHS Digital for purposes beyond care, such as HES, through the national opt-out programme.^29^ HES is an important source of data relating to health service interaction in secondary care. There are three significant limitations that are relevant to this study.

First, referral to liaison psychiatry services cannot be reliably determined from HES. A new episode is not generated by such a referral—the patient remains within the care of the acute hospital consultant—and contact with a different consultant-led team in liaison psychiatry is not represented within an episode.

Second, it is suggested that mental health diagnoses recorded in routinely collected NHS data, such as HES, exhibit variable accuracy with respect to the true diagnosis.^30^

Third, patient interactions with primary care services are not included in HES. Such data are required to match patients by defined characteristics and to determine the care delivered in primary care following a general hospital admission that leads to a liaison psychiatry referral.

To address the first limitation, clinical databases controlled by the mental health trusts that provide liaison psychiatry services will be used. Such databases contain patient data relating to care provided by liaison psychiatry services and can be used in conjunction with HES data to determine whether a patient was referred to a liaison psychiatry service during a hospital admission. The main challenges with the use of such databases are data quality and the heterogeneous processes by which data access is negotiated and administered within different organisations.

To address the second and third limitation, data relating to primary care is required for each patient. Although the Clinical Practice Research Datalink database^31^ is widely used for primary care research in the UK, it has a major drawback for this study—limited numbers and geographical coverage of participating primary care organisations at the time of study design. Instead ResearchOne,^32^ a research database controlled by The Phoenix Partnership (TPP), will be used. ResearchOne contains patient data relating to primary care provided by organisations using the SystmOne clinical information system.^33^ SystmOne (34%) and EMIS^34^ (56%) are the most prevalent clinical information systems used by organisations in general practice.^35^ Therefore, many of the patients with episodes in the HES data can be expected to have data relating to their primary care collected by organisations that use SystmOne. ResearchOne contains data for a subset of these patients—patients who: (1) are registered to organisations that use SystmOne and have opted-in to participation in ResearchOne and (2) have not individually opted-out of participation in ResearchOne. The main challenge with the use of ResearchOne is the inability to determine a priori the numbers and geographical coverage of organisations that provide primary care to patients attending the hospitals chosen for the study, and the resultant ability to match HES data to corresponding ResearchOne data for each patient.

Patient data from these three sources will be linked to construct patient care pathways that span primary and secondary care settings. Linkage will be undertaken by NHS Digital. Each data source will generate two unique references for each patient: (1) a pseudonym—generated by applying a one-way cryptographic hash function (SHA-512) to an input that comprises a cryptographic salt and their NHS number and (2) a source-specific identifier. For a patient with a given NHS number, each data source will generate the same pseudonym but a different source-specific identifier. Both the pseudonym and source-specific identifier generated for each patient will be specific to the study. Pseudonyms will be used by NHS Digital to: (1) communicate to data sources of those patients for whom data are required and (2) generate mappings between different source-specific identifiers for each patient. Data sources will provide the required patient data to the research team, including only the source-specific identifier as the unique reference for each patient. The mappings generated by NHS Digital will be provided to the research team and used to determine the data that relate to each patient across the data received from different sources.

### Data extraction

Based on the results from earlier stages of the LP MAESTRO project, we will identify at least two and up to six configurations that best represent patterns of liaison psychiatry service across England. Defining features of such configurations will include, for example, staff mix, availability of specialist teams (eg, age-related, self-harm), hours of service provided by the specialist team and source of referrals (predominantly ED, predominantly ward, specialist services and so on). We will sample purposively to obtain 2–4 services of each type (depending on availability). Data will be extracted for patients attending the hospitals with these service elements in a 1-year index period and also for patients attending hospitals identified as not having a liaison psychiatry service in the same period. Financial year 2013–2014 was selected as the index period as it represented the latest complete year for which data was available from NHS Digital at the time of study design. Numbers of accident and emergency (A&E) attendances and inpatient admissions in the index period to estimate sample size are not publicly available at hospital level. However, numbers are published by NHS Digital at trust level,^36 37^ where one trust operates one or more hospitals. These trust-level figures provide an indicative upper bound on the A&E attendances and inpatient admissions that can be expected at any hospital operated by that trust in a given year.

Relevant variables extracted for each patient from the sources will include demographic variables (eg, age, carer support, index of multiple deprivation—a measure of locality deprivation), clinical variables (eg, diagnosis, medications) and health service utilisation variables (eg, inpatient days, general practitioner (GP) appointments, major procedures). One of the novelties of our approach is the use of variables obtained from primary and secondary care settings to tackle the substantial challenge that comes from indication bias; for example, we will use variables obtained from ResearchOne to define healthcare usage in primary care for the year before referral (2013), as a way of ensuring that outcomes in the year after referral (2015) are not attributed to easily identifiable pre-existing characteristics (case complexity) that are confounded with likelihood of referral.

Patient care pathways for patients attending hospitals using liaison psychiatry services in each configuration will be constructed to provide a view of health and healthcare across both primary and secondary care. Pathways will be constructed for patients for a period of 12 months following their index (first) hospital admission in the index period. The cost of each pathway to the healthcare sector will then be calculated using national data sources (see below). We will adopt a whole system perspective in order to determine if there is an association between the configuration of liaison psychiatry services and healthcare utilisation by patients. Metrics including emergency admissions, occupied bed days and length of stay will be analysed by age band.

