**Methods and analysis:**

The project will use three data sources: (1) Hospital Episode Statistics (HES), a database controlled by NHS Digital that contains patient data relating to emergency department (ED), inpatient and outpatient episodes at hospitals in England; (2) ResearchOne, a research database controlled by The Phoenix Partnership (TPP) that contains patient data relating to primary care provided by organisations using the SystmOne clinical information system and (3) clinical databases controlled by mental health trusts that contain patient data relating to care provided by liaison psychiatry services. We will link patient data from these sources to construct care pathways for patients who have been admitted to a particular hospital and determine those patients who have been seen by a liaison psychiatry service during their admission.

Patient care pathways will form the basis of a matched cohort design to test the effectiveness of liaison intervention. We will combine healthcare utilisation within care pathways using cost figures from national databases. We will compare the cost of each care pathway and the impact of a broad set of health-related outcomes to obtain preliminary estimates of cost-effectiveness for liaison psychiatry services. We will carry out an exploratory incremental cost-effectiveness analysis from a whole system perspective.

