## Methods and analysis

### Study design

Retrospective cohort design, comparing outcomes for patients admitted to hospital and seen by a liaison psychiatry service with two control groups—the first is a patient group who were admitted to the same hospital in the same study period and matched on hospital inpatient and primary care data, but were not seen by the liaison psychiatry service. Because such a design could not entirely exclude confounding by indication, we will use a second matched patient group who had been admitted to a different hospital without a liaison psychiatry service in the same study period. This second group will also be matched using data from hospital and primary care records; however, they will not have been selected on the basis of whether the responsible (acute hospital) consultant had made a decision about liaison psychiatry referral.

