### Data analysis

We will build a standard regression model to estimate the relation between healthcare utilisation and key variables capturing the configuration of liaison psychiatry services. The dependent variable in this model will therefore be the total costs of any identified healthcare utilisation derived from factors such as inpatient days, readmission rates, ED attendances and GP visits combined with reference costs. These reference costs will be valued using national sources, including the Department of Health Reference Costs^38^ and Personal Social Services Research Institute Costs for Health and Social Care.^39^ Where these are not available, local costs will be assigned. We will choose the most appropriate base year for the analysis and adjust appropriately for the effects of inflation across years. The quantum of the liaison psychiatry service provision will be captured by already collected data related to structure and process, for example, staffing levels and contact time after referral. We will adjust for referral indication bias, either by matching for covariates or by propensity scoring.

Sample size is difficult to estimate because we have so little available data on outcomes for different service types and different patient groups. Suppose we identify six main service configurations and recruit two liaison psychiatry services for each (total n=12). For less common conditions we might expect to see one referral per week per service=100 in total in the year. For more common conditions we might perhaps see one referral per day or 600–800 in the year. These numbers will allow us to estimate the costs and cost-effectiveness of liaison psychiatry services with substantially greater precision than has been achieved to date, for example, by the RAID evaluation.

The way in which components of general hospital, general mental health and liaison psychiatry services interact with each other is complex and a key part of the project will be to determine how to capture this complexity into a set of measures for inclusion in the model.

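### Exposed patients must stay until they are seen while controls need not, so length of stay and bed-day costs counted from admission carry immortal-time bias of unknown size

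*Protocol article*

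**What the plan says.** Only the protocol article is available. Five of its statements bear on this point.

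- **Exposure.** The abstract says that linkage will "determine those patients who have been seen by a liaison psychiatry service during their admission". Exposure is therefore acquired at some point after admission. The Discussion limits the evaluation to inpatient work.
- **Controls.** Under Study design, the first group was admitted to the same hospital and is "matched on hospital inpatient and primary care data, but were not seen by the liaison psychiatry service". The second comes from hospitals with no service: "This second group will also be matched using data from hospital and primary care records".
- **Clock.** Under Data extraction: "Pathways will be constructed for patients for a period of 12 months following their index (first) hospital admission in the index period".
- **Outcomes.** The same section adds: "Metrics including emergency admissions, occupied bed days and length of stay will be analysed by age band". Under Data analysis, total cost is "derived from factors such as inpatient days, readmission rates, ED attendances and GP visits combined with reference costs". The economic model is to relate cost to length of stay, re-admission and life years lost.
- **Bias control.** Data analysis offers covariate matching or a propensity score against referral indication. Nothing is said about the timing of contact.

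Data extraction also speaks of outcomes in the year after referral. Controls have no referral date, and none is assigned to them.

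**The concern.** A patient can be seen on the ward only while still an inpatient. The days from admission to contact are therefore guaranteed to the exposed group, and long stays are over-represented in it, because a longer stay gives more opportunity to be seen. Controls face no such condition. With the clock at admission, the pre-contact days count as outcome for the exposed group.

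Two patients with identical records at admission still differ in this way, so matching on baseline characteristics does not help. The second control group was added to deal with selection by the referring consultant, but its members are not aligned on day of stay either. Agreement between the two control groups would therefore be no reassurance on this point.

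The Introduction names shorter stay as the route to the claimed savings, and it justifies the study by the need to confirm or refute such claims. A true reduction smaller than the artefact would be hidden or reversed, and a larger sample would only make the wrong answer more precise.

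**Working it through.** The article states no mean or SD of stay, no day of contact and no expected effect, so there is no figure of its own to reproduce. The check asks what length-of-stay ratio a service with **no effect** would show under unaligned comparison.

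**Input from the article:** share of inpatients seen, p = 1%–5% (Introduction).
**Assumed:** shape of the stay distribution, timing of contact, and other bed days in the year.

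**1. Exponential stays (rate λ), contact at constant hazard h, seen if contact precedes discharge.**

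- p = h/(λ+h).
- Mean stay if seen = 1/(λ+h) + 1/λ. Mean if not seen = 1/(λ+h). Mean of all patients = 1/λ.
- Ratio to all comparable patients (second control group) = 2 − p.
- Ratio to unseen patients (first control group) = 2 + p/(1−p).

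| p | vs second group | vs first group |
|---|---|---|
| 1% | 1.99 | 2.01 |
| 5% | 1.95 | 2.05 |
| 20% | 1.80 | 2.25 |
| 50% | 1.50 | 3.00 |

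The last two rows are included because the share seen among patients resembling those referred may exceed the share of all admissions.

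**2. Other spreads of stay, constant hazard.** For rare contact the ratio tends to 1 + CV². Simulation used 2 million gamma or lognormal stays per scenario. The last column gives the range over both distributions, both control groups and p = 1% and 5%.

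| CV | 1 + CV² | simulated ratio |
|---|---|---|
| 0.5 | 1.25 | 1.24–1.26 |
| 0.75 | 1.56 | 1.53–1.58 |
| 1 | 2.00 | 1.91–2.06 |
| 1.25 | 2.56 | 2.35–2.67 |
| 1.5 | 3.25 | 2.83–3.45 |

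**3. Contact on a fixed day d, exponential stays of mean m, against all comparable patients.** Ratio = 1 + d/m.

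- Day 0: 1.00.
- Day 1 with m = 5, 8, 12: 1.20, 1.125, 1.08.
- Day 3 with m = 5, 8, 12: 1.60, 1.375, 1.25.

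**4. Dilution over 12 months.** If the index stay is doubled and other bed days are r times the unbiased index stay, the bed-day ratio is (2 + r)/(1 + r). For r = 0.5, 1 and 2 this gives 1.67, 1.50 and 1.33. Total cost also includes ED and GP use, which dilutes it further.

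**5. Aligned comparison.** When controls were drawn at random from patients still in hospital on the seen patient's contact day, the null ratio was 0.99–1.01 in every simulated scenario.

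**6. Why aligned controls should be not yet seen rather than never seen.** In the model of step 1, remaining stay from the contact day averages 1/λ for a seen patient. For a patient still in hospital who is never seen later it averages 1/(λ+h). The ratio is 1/(1−p): 1/0.99 = 1.01 to 1/0.95 = 1.05. Selecting on the future leaves a small residual bias.

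**Direction for deaths.** A seen patient cannot have died before contact, whereas a control can. For life years lost the same misalignment therefore favours the service.

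**The case against.** **The contrast is assembled from several sections.** The sentence on length of stay follows one about service configuration, and the regression under Data analysis also relates cost to configuration. Comparing all attenders across configurations creates no immortal time. This stands, and it limits the point to the seen-versus-control contrast. That contrast is nevertheless the stated design, and the abstract rests the test of effectiveness on it.

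**The argument is from silence in a condensed article.** The hospital data used for matching are not itemised, and a fuller plan may contain an alignment rule. The article does not rule one out. But it does state the exposure definition, both control definitions, the start of the clock and the outcomes, and following these as written produces the bias. Matching on total stay would not repair it, since that conditions on the outcome. The phrase about the year after referral does not repair it either, since controls have no such date.

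**The size is assumed.** This stands. A reader might infer that a useless service would appear to double length of stay. The documents do not support that as a result: it needs a CV near 1, a constant contact hazard and few patients seen. Early contact is plausible, since Data extraction allows for services whose referrals come mainly from the ED, and the ratio would then be near 1.

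**The estimates are preliminary and the study is retrospective.** True, and alignment can still be chosen at analysis. That makes the change easy to adopt, but it does not make the unaligned estimate valid.

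**Conclusion.** The point holds for the seen-versus-control comparison. As written, the plan biases length of stay and inpatient-day costs against the service, and neither of its stated safeguards removes this. It would vanish only if contact took place effectively at admission.

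The size cannot be fixed from the article. With no true effect, the index-stay ratio is about 2 under exponential stays, constant contact hazard and 1–5% seen. It is about 1.0–1.2 for contact on day 0–1 with a mean stay of 5 days or more, about 1.25 at a CV of 0.5, and above 3 in most scenarios at a CV of 1.5 (2.83–3.45). A doubled index stay becomes 1.33–1.67 in 12-month bed days under the assumed other use.

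Two wider readings are not supported. The bias does not run against the service on every outcome, because life years lost is biased the other way. Nor does it reach comparisons of all attenders across service configurations.

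**What to change.** 1. Obtain the referral or first-contact date from the mental health trust databases and name it in the data requests. The article does not say that this field is available, and it names data quality as a main challenge with these databases, so completeness should be checked first.
2. For each seen patient, draw both control groups from matched patients still in hospital and not yet seen on the same day of stay. Give each control that day as its index date.
3. Analyse remaining length of stay from that day, and costs and outcomes over the 12 months from that day.
4. State in advance how first-group controls who are seen later are handled. Censoring at contact is one option, on the assumption that it is uninformative given the matching variables. An equivalent analysis with time-varying exposure is another.
5. Do not present unaligned admission-to-discharge stay as an effect estimate.
6. Reconcile the two descriptions of follow-up under Data extraction: from index admission, and in the year after referral.

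The cost is a little more analysis work, dependence on the quality of contact dates, and loss of very short stays from the control pool.
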